## Abstract

**Background:**

Arterial hypertension has a direct association with endothelial dysfunction and major cardiovascular events. There is evidence showing the benefits of aerobic exercise on flow-mediated dilation (FMD) in hypertensive individuals but little is known about the effect of autonomic nervous system (ANS) activation on FMD of the brachial artery in response to different types of exercise in this specific population. This study aims to examine the effects of ANS activation on FMD of the brachial artery in response to exercise in hypertensive individuals following a session of different types of exercise including aerobic exercise (AE), resistance exercise (RE), or combined exercise (CE).

**Methods:**

Thirty-nine hypertensive volunteers aged 35 to 55 years will be randomly assigned to two exercise sessions: AE (40 min on a cycle ergometer at 60% of HR reserve), RE (4 lower limb sets with 12 repetitions at 60% 1-RM for 40 min), or CE (RE for 20 min + AE for 20 min). Each exercise group will be randomized to receive either an α1-adrenergic blocker (doxazosin 0.05 mg/kg^−1^) or placebo. Ultrasound measurement of FMD is performed 10 min before and 10, 40, and 70 min after exercise. ANS activation is monitored using a Finometer and measurements are taken during 10 min before each FMD assessment. Arterial stiffness is assessed by pulse wave velocity (PWV) analysis using a Complior device.

**Discussion:**

We expect to demonstrate the effect of ANS activation on FMD of the brachial artery in hypertensive individuals in response to different types of exercise. This study may give some insight on how to improve exercise prescription for hypertension management.

**Trial registration:**

https://clinicaltrials.gov and ID "NCT04371757". Registered on May 1, 2020.

**Supplementary Information:**

The online version contains supplementary material available at 10.1186/s13063-021-05516-x.

## Introduction

Endothelial dysfunction precedes atherosclerosis [1]. Endothelial cells play an important role in modulating vascular angiogenesis and vascular tone and permeability and mediating inflammatory responses and homeostasis [2]. This function of vascular protection is largely attributed to nitric oxide endothelial synthase, an enzyme responsible for nitric oxide (NO) synthesis in the vascular endothelium [2].

Endothelial dysfunction is characterized by a reduction of local NO bioavailability and/or insufficient vasomotor response that occur in certain conditions including arterial hypertension [3], diabetes mellitus [4], obesity [5], dyslipidemia [6], metabolic syndrome [7], aging [8], menopause [9], and sedentary lifestyle [10]. Flow-mediated dilation (FMD) of the brachial artery is an indirect non-invasive technique to assess endothelial function and is chiefly dependent on *NO availability* [11]. Since a*cute* post-*exercise changes in vascular function* may also predict long-term adaptations [12] the acute response to exercise has been widely studied [3, 13].

Lifestyle changes including regular physical exercise are recommended as part of the therapeutic approach for hypertension management [14, 15]. Factors most commonly associated with potential antihypertensive effects and chronic post-exercise changes in endothelial function include reduced autonomic nervous system (ANS) activation [16], balance between vasodilators and vasoconstrictors [17], and reduced levels of the vasoconstrictor endothelin-1 (ET-1) [18].

A meta-analysis that examined cardiovascular risk factors and/or factors associated to established cardiovascular disease found that aerobic and resistance training can potentially improve FMD of the brachial artery [19]. Our research group also found an improvement of 1.45% (95% CI − 0.11 to 3.00) in FMD in response to aerobic training in hypertensive individuals [20]. This finding is clinically relevant as a 1% increase in FMD is correlated to ~ 13% risk reduction of major cardiovascular outcomes [21].

A study of the effects of resistance exercise (RE) on FMD [22] found that a single session of low- and moderate-intensity knee extensions reduced FMD 10, 30, and 60 min after exercise in healthy individuals. Interestingly, FMD did not change when this same set of RE was performed at a high intensity [22], which may indicate an inverse relationship between FMD changes in response to RE as well as to exercise intensity. Our research group has recently reported that a single session of aerobic exercise (AE), lower-limb RE, and CE (AE + RE) at moderate intensity for 40 min did not result in brachial artery FMD changes in hypertensive individuals when measured 10, 40, and 70 min after exercise [23]. In addition, the levels of endothelial microvesicles and substances associated with oxidative stress remained unchanged [23]. Altogether, we can raise the hypothesis that other factors may play a role including exacerbated sympathetic activation in untrained limbs, which may cause vasoconstriction and redirection of blood flow to trained limbs [24, 25], thus potentially competing with the endothelium-dependent vasodilator effect [26].

Alves et al. [27] demonstrated that α1-adrenergic block with phentolamine reduced blood flow in the forearm when compared to placebo during a handgrip exercise session in individuals with heart failure. It has been proposed that exacerbated sympathetic activation plays an important part in the development and maintenance of arterial hypertension [28], so we postulate that following an acute exercise session sympathetic activation potentiates vasoconstriction and may compete with endothelium-dependent vasodilation effects in hypertensive individuals.

In view of inconsistent findings of the acute effects of different types of exercise on FMD in healthy and hypertensive individuals as well as the scarcity of data of the effects of ANS activation on vascular reactivity in response to exercise in hypertensive individuals, we designed a randomized clinical trial with the primary objective of examining the effects of ANS activation on FMD of the brachial artery in response to acute exercise (AE, lower-limb RE, and CE) in hypertensive individuals. Table 1 summarizes the study objectives.

**Table 1 Tab1:** Study objectives

**Primary objective**	
• To compare measurements of FMD of the brachial artery in hypertensive individuals receiving either an α1-adrenergic blocker or placebo after sessions of different types of exercise.	
**Secondary objectives**	
• To compare the effects of ANS activation in hypertensive individuals receiving either an α1-adrenergic blocker or placebo (between-group) in response to acute exercise (aerobic, resistance and combined exercise sessions);	
• To correlate the levels of arterial stiffness and ANS activation and FMD of the brachial artery in hypertensive individuals receiving either an α1-adrenergic blocker or placebo in response to acute exercise (aerobic, resistance, and combined exercise sessions).	

*FMD* flow-mediated dilation, *ANS* autonomic nervous system

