### Visits 3 and 4: α1-adrenergic receptor blockage, assessment of endothelial function, autonomic nervous system activation, and exercise intervention

#### α1-adrenergic receptor blockage

α1-adrenergic blockage is used to assess the effects of sympathetic nervous system (SNS) activation on FMD in response to exercise as described in the literature [26]. Since prazosin is no longer available in Brazil, its analog doxazosin is used in this study [34]. Briefly, 90 min before the start of the exercise intervention, the volunteers are asked to take a tablet containing either placebo (microcrystalline cellulose) or an *α*1-adrenergic blocker (doxazosin 0.05 mg kg^−1^ of body weight) and to lie down and rest. This dose of an *α*1-adrenergic blocker has been reported as being able to block 80% of α1-adrenergic receptors in studies of sympathetic activation and vascular responses [35–37].

An independent researcher blinded to the study intervention gives a tablet to the volunteer on the day of the exercise session according to previous random assignment.

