#### Evaluation of autonomic nervous system activation

ANS activation is evaluated through heart rate variability (HRV) and blood pressure variability (BPV) as described by Atala et al. [40]. Data are collected through continuous non-invasive measurements of pressure waves using digital photoplethysmography (Finometer®, Finapres Medical System BV, Netherland). A cuff device is worn on the middle finger of the right hand coupled to an analog-to-digital converter (AT/MCA-CODAS, DATAC Instruments Inc., Akron, Ohio, USA). Continuous signal sampling acquisition is obtained at 1000 Hz after resting (lying down for 10 min) before FMD. The readings are made for 10 min before forearm cuff inflation for all volunteers either on the placebo or α1-adrenergic blocker groups.

Data are recorded into BeatsScope® (Smart Medical, Gloucestershire, United Kingdom) and LabChart® (ADInstruments, Sydney, Australia) software programs for data analysis of histograms showing BPV and pulse interval series (RR interval) for power spectrum analysis (HRV). All heartbeats are identified through a specialized algorithm using MAT-LAB MT (MATLAB 6.0, Mathworks, USA) with automatic detection of systolic and diastolic pressure wave events. Pulse intervals (PIs) are calculated as the difference between start and end points of the cycle (PI = time point 1 − time point 0). For the time-domain analysis of HRV and BPV data, such as spectrum composition (fast Fourier transform), the CardioSeries® software program is used (www.danielpenteado.com/cardioseries). This analysis requires the removal of transient and discrepant elements and interpolation of consecutive fragments of a time series. The following spectral frequencies are evaluated: very low frequency (VLF, 0.007–0.04 Hz); low frequency (LF, 0.04–0.15 Hz); high frequency (HF, 0.15–0.4 Hz); and total power (TP, VLF + LF + HF). Spontaneous baroreflex sensitivity (SBE) is inferred by the square root of (LF/HRV m^2^)/(LF/BPV m^2^) [40].

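### Under α1-blockade, blood pressure variability and the baroreflex index do not measure sympathetic activation on the placebo scale, so the drug-placebo contrast in these indices needs a different label

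*Protocol article*

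**What the plan says.** Table 1 lists two secondary objectives that use autonomic (ANS) activation. The first is "To compare the effects of ANS activation in hypertensive individuals receiving either an α1-adrenergic blocker or placebo (between-group) in response to acute exercise". The second correlates arterial stiffness, ANS activation and brachial FMD under blocker or placebo.

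The section on evaluating ANS activation fixes the measure: "ANS activation is evaluated through heart rate variability (HRV) and blood pressure variability (BPV"). It adds a baroreflex index: "Spontaneous baroreflex sensitivity (SBE) is inferred by the square root of (LF/HRV m^2^)/(LF/BPV m^2"). Recording is the same in both conditions: "The readings are made for 10 min before forearm cuff inflation for all volunteers either on the placebo or α1-adrenergic blocker groups". No measure upstream of the vascular receptor is named.

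The section on α1-adrenergic receptor blockage gives the drug's role, "α1-adrenergic blockage is used to assess the effects of sympathetic nervous system (SNS) activation on FMD in response to exercise", and says that the dose has been "reported as being able to block 80% of α1-adrenergic receptors in studies of sympathetic activation and vascular responses". The tablet is taken "90 min before the start of the exercise intervention". The Introduction states the assumed pathway: "sympathetic activation potentiates vasoconstriction and may compete with endothelium-dependent vasodilation effects in hypertensive individuals".

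Each volunteer attends two sessions, 5 to 7 days apart, with blocker and placebo in random order (Randomization and blinding; Reproducibility of FMD).

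**The concern.** The protocol introduces the blocker as a probe of what sympathetic activity does to the vessel. Table 1 then compares ANS activation between blocker and placebo, using a readout that is partly a vascular response. The drug acts between the quantity of interest (sympathetic activity) and part of the signal that is meant to measure it (pressure oscillations). A fall in BPV under the drug could mean less sympathetic activity, or the same or more activity that reaches the vessel less well. The protocol neither separates these cases nor says that BPV is to be read differently under blockade.

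Two conclusions are at stake. The trial could report that sympathetic activation after exercise is lower with the drug when only its transmission was reduced; if outflow rose in response to lower pressure, the sign would be wrong. And if BPV is related to FMD with both conditions together, the drug can move both variables and create an association that resembles the trial's hypothesis.

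**Working it through.** The protocol gives no figure on this point to reproduce. The check is a reading of the passages plus an illustration.

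**Inputs from the protocol**
- Block of α1-receptors: 80%, partial.
- Baroreflex index: read as √(LF-HRV ÷ LF-BPV), where LF is low-frequency power.
- Timing: tablet 90 min before exercise; first FMD 10 min before exercise; ANS recording in the 10 min before each FMD.

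**Assumptions, not in the protocol**
- Pressure oscillations depend on α1-mediated vasoconstriction. This is consistent with the Introduction and the blockage section, but neither says so.
- Transmission is linear, with gain g = 1 − b, where b is the share of the vascular response lost. Receptor block and lost response need not be equal, so a range of b is shown.
- Sympathetic activity is identical in the two sessions.

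**Step 1: size of the distortion.** Oscillation amplitude scales with g, so LF-BPV power scales with g². With LF-HRV unchanged, the baroreflex index scales with √(1/g²) = 1/g.

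| b | g | LF-BPV power relative to placebo (g²) | Fall | Baroreflex index factor (1/g) |
|---|---|---|---|---|
| 20% | 0.8 | 0.64 | 36% | 1.25 |
| 50% | 0.5 | 0.25 | 75% | 2.0 |
| 60% | 0.4 | 0.16 | 84% | 2.5 |
| 70% | 0.3 | 0.09 | 91% | 3.3 |
| 80% | 0.2 | 0.04 | 96% | 5.0 |

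The last column is an upper case. If LF-HRV fell in the same proportion as LF-BPV, the index would not move (factor 1), but LF-HRV would then carry the drug effect.

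**Step 2: when the sign is wrong.** Let sympathetic amplitude under the drug be r times its placebo value. LF-BPV power is then (g × r)² of placebo. It still reads lower whenever r < 1/g, that is, for any rise smaller than 1.25-fold at b = 20% or 2-fold at b = 50%.

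**Step 3: does change from pre-exercise remove it?** The pre-exercise recording starts about 90 − 10 − 10 = 70 min after the tablet, so it is also under the drug. If exercise multiplies the amplitude s by k, the change in power is s²(k² − 1) under placebo and g²s²(k² − 1) under the drug. The simple change is still scaled by g². The ratio of post- to pre-exercise power is k² in both sessions, but only if blockade is constant up to the 70-min reading. The protocol does not state this.

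**Step 4: HRV.** HRV comes from pulse intervals, a cardiac signal that the vascular α1-receptor does not generate. A drug-placebo difference in HRV can be a real autonomic difference. The Additional information section lists low blood pressure as a possible drug effect, so such a difference may be a reflex to the drug and not a response to exercise alone.

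**The case against.** The strongest defence is the wording. Table 1 speaks of the effects of ANS activation, and the blockage section uses the drug to expose those effects. On that reading, a weaker end-organ response under blockade is the intended contrast. This has some force, but the downstream vascular outcome is FMD, already the primary objective, and the ANS data are the HRV and BPV indices. If the phrase is ambiguous, restating it is still the remedy.

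It is also fair to say that the protocol names no single sympathetic index, that the dependence of LF-BPV on α1 tone is imported physiology, and that the trial is exploratory with only secondary objectives touched. All of this stands and limits the point.

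Four stronger readings are tempting, and the document does not support them:
- *No drug-placebo difference in the ANS readout can be a difference in ANS activation.* Not so for HRV, which may show a real, drug-induced difference.
- *The drug switches the pathway off.* The stated block is partial, and the 96% fall is an illustration, not a forecast.
- *The plan pools the two conditions in the correlation.* Neither Table 1 nor the Statistical analysis section says so; the latter only names the Pearson and Spearman methods.
- *Both secondary objectives should move to the placebo session.* That would discard a randomised within-person comparison that is valid as an estimate of what the drug does to the indices.

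**Conclusion.** The point holds for BPV and for the baroreflex index. Between blocker and placebo sessions, a difference in these cannot be read as a difference in sympathetic activation, and a simple change from the pre-exercise recording does not repair this. It does not invalidate HRV, which needs the narrower caution that a difference may be a reflex to the drug.

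The size is unknown. In the illustration, LF-BPV power falls by 36% to 96% and the baroreflex index rises by a factor of 1.25 to 5 with no change in neural activity. These figures rest on linear transmission, unchanged outflow and, for the index, unchanged LF-HRV. The conclusion itself needs only the assumption that pressure oscillations depend on α1-mediated vasoconstriction. The comparison of FMD between blocker and placebo is not affected. What changes is what the two secondary objectives can conclude.

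**What to change.** 1. Keep the randomised within-person contrast, but restate the first secondary objective as the effect of α1-blockade on HRV and BPV indices after exercise.
2. State that conclusions about sympathetic activation from BPV and the baroreflex index will come from placebo sessions only, and that a drug-placebo difference in HRV may include a reflex response to the drug.
3. Run the ANS-FMD correlation separately by condition, not pooled, with the placebo session named as the one that addresses the hypothesis. Within the blocker session, differences between volunteers in achieved blockade could drive both variables, so that correlation should be reported with this caveat.

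The cost is wording in the objectives and the analysis text; no measurement is added. The downside is that the sympathetic inference and the main ANS-FMD association use one session per volunteer: 39 sessions at the planned enrolment (13 per exercise group), or 30 if completion falls to the calculated 10 per group.

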## Methods/design

### Study setting

This is a randomized, double-blind (blinded to the drug/placebo but not to the type of exercise) parallel-group exploratory clinical trial with a group allocation rate of 70% for the calculated sample. Our study was approved by the local ethics committee (#5678/19) and it will be conducted at Instituto de Cardiologia do Rio Grande do Sul/Fundação Universitária de Cardiologia (ICFUC) – study site. We will use radio, television, social media advertisements to recruit volunteers as well as invitations through phone calls to eligible individuals following a review of medical records from the hospital where the study will be held. All eligible individuals must read and sign a free and informed consent (supplementary material) before entering the study. The study protocol is being developed following the principles of the Declaration of Helsinki. All study information is confidential; volunteers’ names will be kept confidential and all data obtained in the study will be used for academic purposes only. Research data will be stored for five years and then discarded according to the guidelines of CNS Resolution No. 466/12. Finally, any adverse effect during the research will be reported to the local ethics committee that will have access to the adverse results and will make the decision in relation to terminating the study, if applicable. Relevant protocol amendments such as changes to eligibility criteria, unwanted effects, violation of the rights of volunteers, registration, and analysis of results as well as contributions of the study investigators will be reported to the research project coordinator ([name]) and then to the local ethics committee. The study protocol will be updated in the clinical trial registry if applicable.

The study will not receive financial support from any institution, including from ICFUC. Also, ICFUC was not involved in the study design and will not be involved in either data collection, management, analysis, and interpretation or manuscript writing and any decisions regarding submission of articles for publication.

The coordinating center and trial steering committee are tasked with recordkeeping and reviewing ethical issues. The Research Unit (UP/ICFUC) is responsible for registering clinical trials and managing the registration and provides daily support to any issues regarding trial registration. The local ethics committee (EC/ICFUC) is an independent board consisting of academics and representatives of civil society that meet once a month to grant ethical approval for research projects and evaluate research proposals for their importance to society. In addition, research integrity and timeline are overviewed by ICFUC Health Sciences Graduate Program Advisory Committee.

### Trial status

The study is registered on “www.clinicaltrials.gov” (ID: NCT04371757), the anticipated primary completion date is December 20, 2020, and the expected date for full completion of the study (analysis and presentation of results) is December 23, 2021. However, because of the COVID-19 pandemic worsening in Brazil, all clinical research projects have been temporarily suspended at ICFUC (the study site). The expected date for resumption of research activities is November 26, 2021, and the expected completion date is November 25, 2022.

This study protocol has a single version with no updates or addenda since it was registered with ClinicalTrials (“First Posted: May 1, 2020 and Last Update Posted: May 1, 2020”).

### Eligibility criteria

Recruitment will be through on-site screening, media postings, and patient databases. Thus, hypertensive male and female individuals aged 35 to 55 years receiving health care at the study site, using anti-hypertensive drugs, who do not engage in regular physical exercise (≥ 2 sessions per week) are eligible to participate. Exclusion criteria are individuals with diabetes mellitus; chronic renal failure; body mass index (BMI) ≥ 35 kg/m^2^; coronary artery disease; heart failure; users of beta-blockers and/or alpha-blockers; smoking; lower limb injuries that prevent them from engaging in the study intervention; and females aged 35 to 55 with menopause. If doxazosin induces a change in exercise workload or a reduction in blood pressure to levels that would affect exercise performance, the volunteer will be excluded from the study. If a volunteer drops out before completing both study interventions (α1-adrenergic blocker or placebo), we will make an effort to reach them and find out the reasons behind it. If their decision is final, it will be considered “subject withdrawal” and their data will be excluded from the final analyses.

### Sample size

The sample size is calculated according to Atkinson et al. [26]. In their study, they compared endothelium-dependent vasodilation (by FMD) after a single session of moderate-intensity AE for 30 min in healthy individuals receiving an α1-adrenergic blocker (prazosin 0.05 mg/kg^−1^) or placebo and reported a *difference in means of* 3.1% with standard deviations (SDs) of 1.13% for placebo and 1.91% for prazosin. For finding a similar difference in FMD (3.1%) between these two conditions (α1-adrenergic receptor block versus placebo) after our protocol’s exercise session (AE, RE, and CE) considering *α* = 0.05 and 80% power, a sample of five volunteers per group (*n* = 15) is required.

For a comparison of FMD measurements among exercise types (AE, RE, and CE), our sample calculation is based on pre-exercise SD (1.18%) and post-exercise SD (1.91%) for the prazosin group as described by Atkinson et al. Thus, to find a difference in FMD of 1.62% considering *α* = 0.05 and 80% power, a sample of 10 individuals per group (*n* = 30) is required. Assuming a 30% loss, a sample of 39 individuals would be required (*n* = 13 per group).

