### Randomization and blinding

Randomization of the study interventions (exercise groups) as well as assignment to intervention conditions (either an α1-adrenergic blocker or placebo) are carried out *using computer program* (www.randomization.com) with a coded numeric distribution. Allocation concealment is guaranteed by using sealed envelopes; the random allocation of volunteers is kept in an inaccessible place and researchers will not have a priori knowledge of the intervention assignment to each volunteer. Randomization is carried out by an independent researcher not involved with the study.

Considering the volunteers’ age group (35 to 55 years) and that comparison analyses (primary and secondary outcomes) involve testing for baseline differences, we are conducting simple randomization divided into two steps: (1) by exercise type (AE, RE, or CE) and (2) the order of condition (either placebo or α1-adrenergic blocker). All volunteers are blinded to the intervention allocation and will only have access to this information after a baseline evaluation. They are also blinded to the intervention condition (either placebo or α1-adrenergic blockade). The researchers responsible for the analyses of data are blinded to the intervention allocation and condition to minimize potential measurement bias. As the medical staff and investigators are not blinded, unblinding will not occur.

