### Statistical analysis

A per-protocol (PP) analysis will be conducted. The Shapiro-Wilk is used to test the normality of data. Values are presented as means ± standard deviations or medians and 95% confidence intervals (95% CIs) according to the distribution of variables. A multivariate analysis of data is performed using the generalized estimation equations (GEE) for repeated measures with Bonferroni’s post hoc. Pearson’s and Spearman’s tests are used to assess potential correlations between variables according to their distribution. Statistical analyses are carried out using the Statistical Package for Social Sciences (SPSS) 24.0. A level of significance of < 0.05 is set for all analyses.

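### The stated 80% power to detect a 1.62% FMD difference among exercise types with 10 per group does not follow from the protocol's own inputs

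*Protocol article*

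**What the plan says.** The Sample size section contains two calculations. The first, for blocker versus placebo, uses a difference of 3.1% with SDs of 1.13% and 1.91% and gives five per group (15 in total). The second opens with "For a comparison of FMD measurements among exercise types (AE, RE, and CE" and takes its variability as follows: "our sample calculation is based on pre-exercise SD (1.18%) and post-exercise SD (1.91%) for the prazosin group". It aims "to find a difference in FMD of 1.62"% at alpha "0.05 and 80% power, a sample of 10 individuals per group", which is 30 in total. The loss allowance is then added: "Assuming a 30% loss, a sample of 39 individuals would be required", or 13 per group. The second calculation therefore sets the size of the trial.

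Under Randomization and blinding, allocation has two steps: "by exercise type (AE, RE, or CE) and (2) the order of condition". Exercise type is thus a between-volunteer factor, and only blocker versus placebo is crossed within a volunteer. The Statistical analysis section plans "generalized estimation equations (GEE) for repeated measures with Bonferroni’s post hoc". It gives no number of post hoc comparisons and does not say which factor they concern. The article states no pre-post correlation, no SD of change and no sidedness of the test.

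**The concern.** The comparison named and the inputs used do not belong together. The spread of FMD before and after exercise in one group is what a before/after test within that group needs, together with a correlation. A comparison of AE, RE and CE needs the between-volunteer SD of whatever is compared: post-exercise FMD, its change, or the blocker-placebo difference.

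The consequence is a stated power that may be well above the real one. A reader who sees 80% power for 1.62% could give a non-significant comparison among exercise types more weight than it deserves.

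**Working it through.** **Inputs** (Sample size section unless noted): difference 1.62%; SDs 1.18% and 1.91%; alpha 0.05, taken as two-sided; power 80%; 10 per group; independent groups (Randomization and blinding). Assumed, because not stated: the pre-post correlation r, and three contrasts for Bonferroni.

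**1. The protocol's own figures, by the two-sample normal formula**

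n per group = 2 × (1.960 + 0.842)² × SD² / difference², with SD² the mean of the two variances and (1.960 + 0.842)² = 7.849.

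- First calculation: SD² = (1.13² + 1.91²)/2 = 2.4625; n = 2 × 7.849 × 2.4625 / 3.1² = 4.02, rounded up to 5. This matches the protocol.
- Second calculation: SD² = (1.18² + 1.91²)/2 = 2.520; n = 2 × 7.849 × 2.520 / 1.62² = 15.1, rounded up to 16. The protocol has 10.

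The formula that returns the first figure does not return the second.

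**2. Two-sample t-test with both SDs**

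SD = √2.520 = 1.588; standardised difference = 1.62/1.588 = 1.02. At 10 per group the noncentrality is 1.62 / (1.588 × √(2/10)) = 2.28, against a critical t of 2.10 on 18 df.

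| n per group | Power |
|---|---|
| 9 (13 × 0.70 = 9.1, i.e. after 30% loss) | 53.0% |
| 10 | 57.9% |
| 13 (no losses) | 70.4% |
| 16 | 79.8% |
| 17 | 82.2% |

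So 17 per group are needed. At 10 per group the difference detectable with 80% power is about 2.1%. A simulated Welch test at 10 per group gives 57.0%. A one-sided test would still need 13 per group.

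**3. Change scores compared between groups**

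SD of change = √(1.18² + 1.91² − 2 × r × 1.18 × 1.91).

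| Assumed r | SD of change | Power at 10 per group |
|---|---|---|
| 0 | 2.245 | 33% |
| 0.3 | 1.920 | 43% |
| 0.5 | 1.669 | 54% |
| 0.7 | 1.373 | 70% |
| 0.8 | 1.198 | 82% |

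**4. One-way ANOVA over three groups**

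With SD 1.588 and extreme means 1.62 apart, power at 10 per group is 47% to 60%, depending on where the middle mean lies.

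**5. What does return about 10**

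- A paired pre-post test within one group: 78% power at r = 0.5 (11 needed) and 85% at r = 0.6 (10 needed). This is not a comparison among exercise types.
- A two-sample t-test with SD 1.18 in both groups: 82.7% at 10 per group. This discards the stated 1.91; with 1.91 in both groups power is 43.5%.
- Change scores with r of about 0.8, which is not stated.

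**6. Multiplicity, on an assumption**

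If Bonferroni covers three pairwise exercise contrasts, alpha = 0.05/3 = 0.0167. Under the reading in step 2, power at 10 per group is 38.5%, 22 per group are needed, and the detectable difference is about 2.5%.

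**The case against.** The best reply is that no single power figure can be read off this document. If the two SDs are the wrong inputs for a between-group test, pooling them to 1.588 has no special standing either. Across the readings above, two-sided power without multiplicity adjustment runs from about 33% to 83%. The planned analysis is GEE on repeated measurements, with three post-exercise FMD readings in each of two sessions, and that could add precision. For example, averaging three readings with an assumed mutual correlation of 0.3 to 0.5 reduces 1.588 to 1.159–1.296 and gives about 84% to 75% at 10 per group. This stands: 58% is one reading and must be labelled so. It does not rescue the claim, because the section invokes no such gain and gives no correlation to support one.

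The objection on Bonferroni also stands. A reader might infer that the analysis corrects over the three exercise pairs, which would make 39% the operative power. The Statistical analysis section does not say this.

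Finally, the primary objective is blocker versus placebo, sized separately at 15. Comparing exercise types head to head is not a separate objective in Table 1, and the trial is already called exploratory. That limits the damage, but an explicit 80% claim that fixes the trial's size still has to follow from its inputs.

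**Conclusion.** The point holds as a mismatch between inputs and comparison. Ten per group with 80% power for 1.62% among exercise types does not follow from what the protocol states. It is recovered only by dropping an SD, by testing a different comparison, or by adding an unstated correlation.

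Its size depends on the reading. Taking the two SDs as those of two independent groups, at two-sided alpha 0.05, power is about 58%, 17 per group are needed and about 2.1% is detectable. Change scores give about 33% to 70% for r from 0 to 0.7. The 39% and 2.5% figures rest on the further assumption of three Bonferroni contrasts.

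Three stronger readings are not supported:
- That the true power is known to be 58% or 39%: the documents do not fix the test, the correlation or the number of contrasts.
- That this error undersizes the blocker-placebo comparison: by the protocol's own figures that needs 15, and 30 exceeds it.
- That the trial plans to claim equivalence of exercise types from a null result: no such analysis is described.

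**What to change.** In the Sample size section:

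1. Remove the claim of 80% power for a 1.62% difference among exercise types.
2. State the test intended, the quantity compared and its between-volunteer SD, any correlation relied on with its source, and whether and over how many contrasts alpha is adjusted.
3. Restate what 10 completers per group provide. Under the two-sample reading: about 58% power for 1.62%, or 80% power for about 2.1%, labelled as assumption-dependent. If three Bonferroni contrasts are intended, say so and give about 39% and about 2.5%. If the sponsor holds a correlation that supports 10 per group, state it and show the calculation.
4. Describe the comparison among exercise types as exploratory, reported as estimates with 95% CIs, and keep blocker versus placebo as the powered comparison.

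The cost is wording only. The stated power becomes less favourable, and no volunteers are added.
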